### Cluster-Randomized Controlled Trial

#### Study Design

The intervention trial aims to test the efficacy of the intervention, primarily with PWUD outcomes, and secondly, at family members and CHW levels. We hypothesize that (1) the intervention will improve PWUD’s service fulfillment along the addiction service continuum, as well as their health outcomes; (2) the intervention will enhance CHWs’ provision of addiction-related service provision for PWUD and support of their family members; and (3) the intervention will improve family members’ support for PWUD’s engagement in the addiction continuum. The trial will be conducted in 3 regions in Vietnam. These regions represent geographical variations in the country. The trial will include 60 CHCs, randomized to either an intervention or control condition. We propose to enroll 720 PWUD and 720 family members (12 families per CHC) as well as 180 CHWs (3 per CHC). Intervention outcomes will be evaluated at baseline and every 3 months after that (Figure 2). We plan to select communes with the highest number of PWUD in each region to ensure adequate participants. The selected CHC in each region will be paired based on the number of PWUD. Within each pair, the CHC will be randomized after baseline.

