#### Sample Size

The study will randomize 60 CHCs (clusters) to intervention and control conditions with a 1:1 ratio. The sample size calculation was based on the primary outcome measure. We propose enrolling 720 PWUD (360 per condition) to ensure we have 80% power at 5% significance level to detect a standardized effect size of 0.41 when comparing the mean change scores of the primary outcome between intervention and control conditions. The proposed sample size accounts for the commune-level clustering, repeated observations within PWUD, and an attrition rate up to 8% for PWUD.

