#### Data Analysis

All participants will be analyzed on an intent-to-treat basis. Descriptive statistics, frequencies for demographic and baseline characteristics, and all the outcome measures will be summarized at baseline by intervention condition. For each study population, generalized linear mixed-effects regression models with appropriate link functions will be used to compare the changes in the primary outcome from baseline between intervention and control groups. Each regression model will include commune- and participant-level random effects to account for dependence within communes and repeated observations within participants. The main effects included in each model are intervention condition, visit, and a condition-by-visit interaction term. Intervention effects on the primary outcomes will be estimated using model contrasts. The preselected demographic and background characteristics (covariates) will be added to evaluate whether the intervention effects on primary outcomes remain significant. The same analytical approach will be applied to each STTR domain score and the secondary outcomes of interest. We also plan to conduct several exploratory data analyses to (1) examine the intervention effect on each STTR fulfillment indicator by subgroup, (2) explore the interrelationship among PWUD’s STTR domains or indicators to identify service gap, and (3) explore the interconnectedness of intervention effects on CHW, PWUD, and family members.

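### Communes are randomised in pairs within region, but the primary model lists no region, pair or pairing variable, so the analysis does not reflect the randomisation

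*Protocol article*

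**What the plan says.** On randomisation, the Study Design section says: "The selected CHC in each region will be paired based on the number of PWUD. Within each pair, the CHC will be randomized after baseline". It says of the regions: "These regions represent geographical variations in the country". The Sample Size section gives the scale: "The study will randomize 60 CHCs (clusters) to intervention and control conditions with a 1:1 ratio". That makes 30 pairs.

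On analysis, the Data Analysis section specifies random effects for commune and for participant, and then: "The main effects included in each model are intervention condition, visit, and a condition-by-visit interaction term". The intervention effect is a contrast in change from baseline. A later step adds covariates chosen in advance, which the article does not name, to see whether the effect stays significant.

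The Sample Size section credits the 720 PWUD with allowing for commune clustering, repeated measurement and attrition of up to 8%. It does not mention pairing.

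**The concern.** The design restricts the randomisation in two ways, by region and by pair. The listed model treats the 60 communes as if they had been allocated freely. When communes in the same stratum tend to change alike, balancing the arms within strata removes that shared variation from the difference between arms. A model without the strata still counts it as error between communes. The standard error it reports is then larger than the true one, intervals are wider than they need be, and the test rejects less than 5% of the time under the null.

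The stake is efficiency, not validity: there is no bias and no inflation of the type I error from this source. There is also a matter of prespecification. If the plan is silent, the choice between an analysis that uses the pairs and one that does not remains open once results are known.

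**Working it through.** **Inputs from the article.** 60 communes, 30 per arm; 12 PWUD per commune; 720 PWUD, 360 per arm; 8% attrition; 80% power; 5% significance (two-sided assumed); standardised effect 0.41 on change scores.

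**Inputs assumed.** The intracluster correlation (ICC) and the share R of between-commune variance in change that region and pair explain. The article gives neither.

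**1. The plan's own sample size.**
- Unclustered n per arm = 2 × [(1.960 + 0.842)/0.41]² = 93.4.
- Retained per arm = 360 × 0.92 = 331.2; retained per commune m = 12 × 0.92 = 11.04.
- Implied design effect = 331.2/93.4 = 3.55; implied ICC = (3.55 − 1)/(11.04 − 1) = 0.25.

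An ICC of 0.25 gives a total of 713 and power of 80.4%. So 720 is attainable without any credit for pairing, but it cannot be verified because the ICC is not stated.

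**2. Variance of a commune's mean change at a design effect of 3.5.**
- ICC = 2.5/10.04 = 0.249.
- v = 0.249 + 0.751/11.04 = 0.317.
- Standard error ignoring pairs = √(2 × 0.317/30) = 0.145.

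**3. Detectable effect with the pairs in the analysis (29 df).** The true standard error is √[2(v − R × ICC)/30].
- R = 0: (2.045 + 0.854) × 0.1454 = 0.422.
- R = 0.3: √[2(0.317 − 0.075)/30] = 0.127, and 2.899 × 0.127 = 0.37.
- R = 0.5: √[2(0.317 − 0.1245)/30] = 0.113, and 2.899 × 0.113 = 0.33.

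**4. Detectable effect with the pairs left out (58 df).** The test still divides by about 0.145, but the estimate varies only with the smaller true standard error. Approximately, the detectable effect is 2.00 × 0.145 + 0.84 × true SE. At R = 0.3 that is 0.290 + 0.107 = 0.397; at R = 0.5 it is 0.290 + 0.095 = 0.385. Simulation of 30 pairs of commune means gives 0.40 and 0.39.

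| R | Unpaired | Paired | True size of unpaired 5% test |
|---|---|---|---|
| 0 | 0.415 | 0.422 | 5.0% |
| 5 to 10% | 0.41 | 0.41 | between 4% and 5% |
| 30% | 0.40 | 0.37 | about 2.7% |
| 50% | 0.39 | 0.33 | 1.3% |

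In terms of power at 0.41, with r the correlation between the mean changes of the two communes in a pair: 79.8% unpaired v 81.3% paired at r = 0.1, 81.0% v 85.6% at r = 0.2, and 82.8% v 90.0% at r = 0.3. R = 0.3 at this design effect corresponds to r = 0.3 × 0.249/0.317 = 0.24.

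At a design effect of 1.5 with R = 0.3, the figures are about 0.27 v 0.26, with a test size of 3.8%.

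**5. Which terms can help.** Take random intercepts for commune and participant, with assumed variances of 0.15, 0.40 and 0.45 (residual). The standard error of the 12-month change contrast is √[2 × (2 × 0.45)/360] = 0.0707. It is the same with no added term, with region as a main effect, or with pair as a main effect, because effects constant over time cancel from a change. Only interactions with visit can absorb differences in change between regions or pairs.

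**The case against.** Four points on the other side have force.

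- **The design's precision is not thrown away.** A reader might infer that leaving out the pairs loses what the pairing bought, or takes power below 80%. Neither follows. Pairing reduces the true variance whatever the model contains, and the sample size claims no gain from it. For the same reason, comparing 0.37 with 0.41 at R = 30% would overstate the gap: the unpaired analysis of a trial that really is paired detects about 0.40.
- **The gain may be nil.** The article says the regions differ geographically. It does not say that they differ in change on the primary score, or that number of PWUD predicts that change. At about 5% explained or less, full pairing gains nothing and costs half the degrees of freedom.
- **The figures need commune-level variation in change to be in the model.** The article does not say whether its random effects are intercepts only. If they are, the numbers in the table do not describe that model.
- **The article is condensed.** Region or commune size may be among the unnamed covariates.

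The first three stand and limit the size of the point. The fourth stands only in part: the article chose to list the terms of the primary model, the list does not match its own randomisation, and the covariates enter only as a later check.

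**Conclusion.** The mismatch between randomisation and primary model is in the text and is certain. Its consequence is a conservative test with some forgone power, of a size the documents do not allow one to fix. Under the assumed range at a design effect of 3.5, the detectable effect could improve by about 0.03 (30% explained) or 0.06 (50% explained), or not at all (10% or less). This rests on a back-solved ICC of about 0.25, an assumed share explained by region and pair, equal commune sizes, and a model that carries commune variation in change. The documents do not support a claim of bias, of an inflated type I error from this source, or of power below plan. It is a cheap improvement that should be made, not a flaw that threatens the result.

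**What to change.** In the primary model, add region and the commune's number of PWUD as fixed effects, each with its interaction with visit. Main effects alone would leave the change-from-baseline contrast as it is. The cost between communes is 2 degrees of freedom for region and 1 for number of PWUD (as a linear term), so 58 − 3 = 55, and the data were needed to form the pairs.

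Full pair and pair-by-visit terms are an alternative that follows the randomisation exactly, at the cost of 29 instead of 58 degrees of freedom. That pays only if pair members change appreciably alike.

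Whichever form is chosen, it should be written into the analysis plan before outcomes are seen. If the strata are left out on purpose, the plan should say so and why.

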#### Ethics Approval

The study protocol was reviewed and approved by the Institutional Review Board of the University of California, Los Angeles (UCLA IRB#20-001594-AM-0001) and the Institutional Review Board in Bio-Medical Research, National Institute of Hygiene & Epidemiology in Vietnam (NIHE IRB VN01057/IORG 0008555; No: NIHE IRB - 28/2022).

## Results

The intervention and assessment instruments have been developed based on the findings from formative studies (in-depth interviews and focus groups). The pilot activities are scheduled for 2023 and followed by the main trial. For the assessment of trial outcomes, we are scheduled to collect data at baseline and at 3-, 6-, 9- and 12-month follow-ups. We will distribute reports based on the baseline data in early 2024. The intervention outcome results will be available within 6 months of the final data collection date, that is, the main study findings are expected to be available by early 2025.

## Discussion

### Expected Outcomes

We anticipate the intervention to be feasible and provide community stakeholders, health professionals, and policy makers with insights for the future establishment and implementation of a community-based addiction service continuum. Community-based service delivery model has been considered a desirable strategy, and the scale-up of accessible and community-led harm reduction services is a global priority [34]. The existing primary health care system in Vietnam provided an opportunity and platform to test an intervention that features the alliance of CHWs and family members to provide a continuum of addiction services for PWUD. If tested effective, the delivery strategies in this study can potentially serve as an example to provide community-based addiction services in other countries. For example, the CHW training package can offer a transferable tool for training primary care providers in addiction disorders in a global context.

Compared to prior work on community-based service delivery models, this study focuses on community partnership rather than each target population, such as PWUD, family members, or CHWs, respectively. We anticipated that improving CHWs’ capacity through intervention training will strengthen their support for PWUD and family members, which will in turn improve addiction service engagement and retention. With the capacity building in the community, we anticipate that the trained CHWs will focus on adapting services across the care continuum to reflect different conditions of individuals and families, potentially enhancing community service delivery with sustainable outcomes.

Another strength of this study is to pay special attention to the vulnerability of family members and the role of family support. We have learned from the existing literature and previous studies that family can be mobilized to become a locally available, trustful, and sustainable support system. We anticipate that our intervention effort will form a partnership between CHWs and family members. Our intervention aims to address the impact of addiction and stigma on families and the burden and challenges faced by family members. The study findings would contribute to the growing body of literature on the role of family support in community-based addiction services and care.

This study has some limitations. First, considering that we integrate various components (eg, in-person sessions, online groups, home visits, and text messages) in the intervention, we will not have the opportunity to assess the effect of each strategy. Second, the intervention program in this study is designed to use the capacity-building approach to train CHWs. The process of training health workers to improve their knowledge and skills to enhance care and services could be too complex to be identified. Third, although the intervention aims to mobilize community health workers and PWUD’s family members to strengthen community partnerships to support addiction services, the study’s outcome assessments and measures are mainly at the individual level.

### Dissemination Plan

The dissemination of study findings will include articles in both Vietnamese and English journals, international conference presentations, and other scholarly channels. Also, we will disseminate study findings to stakeholders to support the development and implementation of health care policies in Vietnam. We will make the intervention training guides, tools, manuals, and materials available to other interested organizations and agencies.

## Appendix

Multimedia Appendix 1 Peer review report by the National Institute on Drug Abuse - Community-Level Health Promotion Study Section - Healthcare Delivery and Methodologies Integrated Review Group - Center for Scientific Review (National Institutes of Health, USA).

## Abbreviations

CHC: commune health center
CHW: community health worker
MAT: medication-assisted therapy
PWUD: people who use drugs
STTR: Seek-Test-Treat-Retain
